## Abstract

**Background:**

Multisystemic Therapy (MST) is an intensive, short, family- and community-based treatment for serious antisocial behaviour and delinquency in youth. It is an emerging intervention for serious juvenile delinquents. However, conclusive evidence on the balance between costs and effects is limited and in fact non-existent for the Netherlands. The aim of this protocol is to describe the design of a study to evaluate the cost-effectiveness of MST as compared to Care-As-Usual (CAU).

**Methods:**

The cost-effectiveness of MST will be assessed through a Randomised Controlled Trial. Primary outcomes aggressive and delinquent behaviour will be assessed with the parent-reported CBCL and adolescent-reported YSR. Health care utilisation, production loss, and quality of life are recorded using the self-report 'Trimbos and iMTA questionnaire on Costs associated with Psychiatric illness' (TiC-P), and with the MOS Short-Form General Health Survey (SF-20) and EuroQol -5D (EQ-5D), respectively. The study aims to enrol 100 clients in both conditions (MST and CAU). Data will be obtained before treatment (T1), immediately after treatment (T2; 5 months after T1) and at follow up (T3; 6 months after the end of the treatment) from a variety of sources, i.e. clients, parents/primary carers, professionals and police records.

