## Methods

### Trial design

The design of this cost-effectiveness study will be described following the CONSORT statement [13]. The study is a supplement to an MST-effectiveness study [14], which concerns a randomized controlled trial (RCT) with a follow-up measurement after 6 months. Participants will be randomly assigned to one of the two groups: MST or Care-As-Usual (CAU). Data will be collected using a standardized self-report questionnaire in a face-to-face situation before treatment (T1), immediately after treatment (T2) and at follow up (T3; 6 months after treatment) among adolescents, parents/primary carers and therapists. Adolescents and their parents will both receive €10 for filling out the questionnaire. The Medical Ethics Committee of Utrecht University approved the study design, protocols, procedures and informed consent. Participation is voluntary and all participants are asked to provide written informed consent at T1.

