### Interventions

**MST**. Multisystemic Therapy (MST) is an intensive, short-term, home- and community- based intervention program for families of youth with severe psychosocial and behavioural problems. It is based on the social ecological theory of Bronfenbrenner [15] and on models of the cause of delinquency [16]. MST is designed to address complex psychosocial problems and provides an alternative treatment for out-of-home placement of children and youth. It uses the various systems in which the adolescent is embedded: family, peer group, school and neighbourhood. In consultation with the members of the family, the therapist identifies a set of treatment goals and assigns the tasks required to accomplish these goals. MST lasts 4 to 6 months and takes the individual needs of the client into account. Therapists are available 7 days a week, 24 hours a day. Each team includes 3–5 therapists who have a caseload of 3–5 clients each.

**CAU**. Care-As-Usual consists of treatments that are already available for adolescents with severe psychosocial and behavioural problems: juvenile justice services, child welfare services, individual adolescent counselling and home-based social services (for instance, parental counselling). Also included and variably implemented across regions are recently developed, evidence-based services such as Functional Family Therapy (FFT) [17] and Multi-Dimensional Family Therapy (MDFT) [18].

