#### Primary outcomes

Primary outcomes of this study include: recidivism and the frequency and seriousness of antisocial behaviour and other types of problems (internalizing problems, substance use). *Recidivism* will be assessed with data of the Research and Policy Database for Judicial Documentation. With this data we will assess the number of arrests, type and severity of offence of adolescents re-offending during the research period.

*Prevalence and seriousness of antisocial behaviour* will be assessed via different informants and instruments. First, parents and adolescents are asked to fill in the 33 items of the Delinquent Behaviour scale and the Aggressive Behaviour scale of the Child Behaviour Checklist (CBCL: 33 items) [19] and the Youth Self Report (YSR: 30 items) [20,21] respectively. For each item, the child’s behaviour has to be rated on a three-point scale, ranging from 0 (never) to 2 (often).

Additionally, adolescents will fill in two subscales of the Self-Report Delinquency scale (SRD) were used to assess self-report delinquency [22]. Adolescents will be asked to indicate on a list of potential delinquent behaviours whether they engaged in the described behaviours during the past 6 months (‘yes’ or ‘no’). The SRD ‘Violent offending’ (5 items) and ‘Property offences’ (10 items) scales will be used.

*Other types of problems* of the adolescent firstly comprise anxiety/depression, withdrawal and somatic complaints. These items will be measured with 25 items of the Youth Self Report [20,21].

In addition substance use (use of alcohol, soft and hard drugs) will be measured with several questions from a Dutch questionnaire used in the study Youth and risky behaviour [23].

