#### Costs items

In addition to change in primary outcomes, the costs of Multisystemic Therapy compared to CAU will be assessed. Cost assessment will be done from a societal perspective, over a time horizon of one year.

Cost components of adolescent antisocial behaviour will be measured by a modified version of the Trimbos/iMTA questionnaire for Costs associated with Psychiatric Illness (TiC-P) [24]. This questionnaire is originally designed to measure direct and indirect costs of mental health problems. For the current study, we adjusted the questionnaire to a version more suitable for assessments of costs related to child antisocial behaviour [25]. We did this mainly by adding items about youth and social care. Direct costs of the interventions as well as indirect costs will be assessed via various informants, namely professionals, parents and adolescents.

*Direct costs* concern use of all resources that is directly related to the intervention and will be estimated through the review of (time) investment of the professionals, including training, overhead, communication with relevant others, and time and travel costs of professionals involved. In addition, direct costs of health and youth care utilization will be assessed via parents (among other things: visits of the adolescent and parent to health and youth care professionals, hospitalizations and residential treatments, contact with judicial authorities and medication use).

*Indirect costs* are characterized as productivity losses, due to time lost from work because of the antisocial behaviour of the adolescent [26]. Data on productivity loss will be collected via the Short Form Health and Labour Questionnaire (SF-HLQ) that is part of the TiC-P [24]. The Short-Form HLQ (SF-HLQ) contains questions about absence from work, reduced efficiency at work and difficulties with job performance.

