### Data collection procedure

Data will be collected using a standardized self-report questionnaire in a face-to-face situation. The questionnaires will be administered before the intervention (T1), directly after the intervention (T2) and six months after the intervention (T3). Adolescents and their parents will both receive €10 for filling out the questionnaire. The therapist will fill out a questionnaire after the treatment has finished (T2). The questionnaires are also available in old Berber for the Berber Moroccan families. In addition, we make use of one Arab translator who will visit all Arab families.

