### Statistical analysis

First, descriptive statistics will be performed to describe the demographic characteristics of the study population.

Second, primary measures of effect will be analysed using within group comparisons (pre-post treatment) and between group comparisons. The latter one will use difference scores (pre-post intervention) after which the treatment effects of the two treatment conditions will be compared. Statistical testing will be done using either the paired t-test or the Wilcoxon signed-rank test for comparisons within the treatment groups and the unpaired t-test or the Mann–Whitney U test for comparisons between the treatment groups.

Third we will describe the mean costs per respondent in both treatment groups. Differences in costs between the intervention group and the control group will presented based on the trial data, and 95% confidence intervals will computed based on bootstrap re-sampling with 5000 replications of the trial data. Separate estimates will be made for different cost categories. For the cost-effectiveness analysis, mean annual societal costs will be linked to the primary measure of effect (Aggressive behaviour and Delinquent behaviour). A cost utility analysis will link the EQ-5d based utilities to the cost.

Fourth, point estimates for the incremental cost-effectiveness and cost utility ratio (ICER) will be computed on complete cost-effect pairs by dividing the incremental societal costs by the incremental effects at 12 months. Uncertainty around the ICERs will be estimated using bootstrapping, generating 5000 replications of the original dataset. A cost-effectiveness acceptability curve (CEAC) will be generated to represent the probability that MST is cost-effective compared to usual care over a range of thresholds [26,36].

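### The last visit falls nominally 11 months after baseline, not at the 12 months used for annual costs and the ICER, and its anchor does not guarantee equal windows in the two arms

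*Protocol article*

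**What the plan says.** The article times the visits in three places. The abstract (Methods) has data collected before treatment, then "immediately after treatment (T2; 5 months after T1) and at follow up (T3; 6 months after the end of the treatment" months-based as shown, with no distinction between arms. Trial design has only "immediately after treatment (T2) and at follow up (T3; 6 months after treatment", and Data collection procedure only "directly after the intervention (T2) and six months after the intervention (T3"; neither gives a time from baseline.

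On treatment length, Interventions states that "MST lasts 4 to 6 months and takes the individual needs of the client into account". For the comparator it says "Care-As-Usual consists of treatments that are already available for adolescents with severe psychosocial and behavioural problems", and lists justice, welfare, counselling and home-based services plus FFT and MDFT in some regions. It gives no duration for any of them.

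Outcome measures allows three measurement moments and no more. The economic analysis nevertheless uses a year. Costs items sets the assessment "over a time horizon of one year". Statistical analysis links yearly societal costs to aggressive and delinquent behaviour and computes the ICER by "dividing the incremental societal costs by the incremental effects at 12 months".

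Primary outcomes has adolescents report, on the Self-Report Delinquency scale (SRD), "whether they engaged in the described behaviours during the past 6 months".

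**The concern.** The ICER and the acceptability curve are the main product of this study. Their numerator is a cumulative cost, so the length of the period over which it builds up matters directly. If the visits stop before 12 months, the yearly cost is either a shorter-period cost with the wrong label or an extrapolation by a rule that the article does not give.

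The anchor raises a second question. Treatment length is determined after randomisation. If it sets when each participant is last seen, it also sets how much cost can be recorded. An arm with longer courses would then show more cost, and utilities measured later, without any treatment effect. Randomisation does not protect against this, although Strengths and limitations relies on it to cancel out confounding.

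The third question is narrower. If T2 comes less than 6 months after T1, the SRD at T2 counts some offending from before treatment.

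**Working it through.** **Inputs.** T2 at 5 months after T1 and T3 at 6 months after end of treatment (abstract); MST duration 4 to 6 months (Interventions); horizon 12 months (Costs items, Statistical analysis); SRD recall 6 months (Primary outcomes). CAU duration: not given.

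**1. Does the schedule reach 12 months?** T3 = treatment duration + 6. Unobserved share = (12 − T3)/12. Factor needed to scale to a year = 12/T3.

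| Treatment duration (months) | T3 (months) | Unobserved share | Scaling factor |
|---|---|---|---|
| 4 | 10 | 2/12 = 16.7% | 12/10 = 1.200 |
| 5 (abstract) | 11 | 1/12 = 8.3% | 12/11 = 1.091 |
| 6 | 12 | 0 | 1.000 |

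The stated 12 months is reproduced only for a full 6-month course. Proportional scaling would assume a flat monthly cost. The intervention's own cost falls in the treatment months, so scaling would spread part of it into a month in which it does not occur.

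**2. Is the anchor consistent?** The abstract places T2 both at end of treatment and at 5 months. For a therapy of 4 to 6 months, both hold only if the course lasts 5 months. Trial design and Data collection procedure keep only the end-of-treatment anchor.

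**3. Are the windows equal between arms?** With T2 at 5 months and treatment taken to end then in both arms, each window is 11 months and the ratio is 11/11 = 1.00. If visits follow each participant's own end of treatment, the answer depends on CAU duration. Assume MST at 11 months and the same monthly cost rate in both arms, so that there is no true difference in rate. The CAU/MST cost ratio is then (CAU duration + 6)/11:

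| Assumed CAU duration (months) | CAU window (months) | CAU/MST cost ratio |
|---|---|---|
| 3 | 9 | 0.82 |
| 4 | 10 | 0.91 |
| 6 | 12 | 1.09 |
| 9 | 15 | 1.36 |
| 12 | 18 | 1.64 |

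These CAU durations are assumptions that show the range. None is in the article.

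**4. SRD recall at T2.** Overlap with the time before T1 = 6 − time of T2. At 5 months this is 1 month; with T2 at the end of a 4-month course, 2 months; of a 6-month course, 0. The overlapping period is also covered by the 6-month recall at T1, so it counts on both sides of the pre-post difference. At T3, 6 months after T2, the recall matches the interval.

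**The case against.** The strongest reply is that this is loose labelling. Eleven months is close to a year, participants with a 6-month course are seen to 12 months, and an article may leave the annualising rule to the full plan. If both arms stop at 11 months, the incremental cost loses only the between-arm difference in month 12, not 8.3% of anyone's costs. This is fair on size, and the absence of an annualising rule is not itself the point. What remains is that the stated visit times and the stated horizon disagree, and the ICER uses the horizon.

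A reader might infer that the observation periods do differ between arms. The article does not support that. The abstract gives one 5-month T2 for everyone, and CAU duration is unstated. Unequal windows are a risk under the end-of-treatment anchor, not a fact.

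A reader might also extend the problem to every outcome. Arrests come from a judicial database and need not stop at T3. Direct intervention costs come from a review of professionals' time. The cost-effectiveness outcomes are scale scores, not totals, although their 12-month label is still affected. QALYs are never mentioned; the article links EQ-5D utilities to cost.

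Finally, a reader might price the missing month from the incarceration costs in Background. Those are literature estimates. The trial will use Dutch guideline prices, and any such sum needs an assumed placement rate. Likewise, a percentage dilution of the SRD contrast would need an assumed offending rate before T1 and independence from later offending. The SRD does not enter the ICER.

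**Conclusion.** The point holds as a contradiction between stated figures. The schedule ends nominally at 11 months, 10 to 12 over the stated MST range, so the one-year horizon, yearly costs and 12-month effects are not what the visits observe. The shortfall is one month nominally and two at most for MST; this is arithmetic on the article's own figures.

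The anchor is also unresolved. Under the end-of-treatment reading, equal windows for questionnaire-based costs and utilities are not guaranteed. How far they could differ cannot be known from the article; the ratios of 0.82 to 1.64 rest on assumed CAU durations and equal monthly rates.

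The SRD overlap at T2, about one month, is real but minor and separate. No euro amount and no size of bias in the ICER can be derived from the article.

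**What to change.** - **Anchor.** State that T2 and T3 are at the same fixed times from T1 in both arms, and make the abstract, Trial design and Data collection procedure agree. T1 is a safer origin than randomisation for the recall periods, because in the North randomisation precedes the appointment for the first questionnaire.
- **Horizon.** Either restate the horizon in Costs items, and the yearly costs and ICER time point in Statistical analysis, as the observed period of about 11 months, or set T3 at 12 months if the parent effectiveness trial's schedule allows.
- **Common window.** Accumulate costs over one window in both arms, and count registry recidivism over that same window.
- **SRD.** Base the comparison on T3, or limit the T2 recall to the time since T1. If T3 moves to 12 months and T2 stays at 5, the recall at T3 starts at month 12 − 6 = 6 and leaves one month uncovered; say so.

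**Cost.** Restating the horizon and truncating to a common window is a change of wording plus an analysis rule; the horizon then falls slightly short of a year. Fixing the visits means that T2 no longer falls exactly at end of treatment for every participant. Moving T3 adds no visit, but the visits belong to the parent trial, so it needs that trial's agreement and may not be cheap.

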**Discussion:**

Studying the cost-effectiveness of this treatment for youth antisocial behaviour is important in order to provide information to policy makers on whether the provision of this intervention represents good value for money. Introducing a cost-effective evidence based programme may result in valuable health gains for moderate costs.

**Trial registration:**

NTR1390

## Background

The direct costs associated with antisocial and delinquent behaviour of adolescents are high. Estimated expenses of incarceration amounted to 114.000 - 250.000 euro per youth per year [1,2]. The degree of recidivism among juveniles who were incarcerated has been estimated to be at least 75% in the first three years after release [3]. Besides direct costs of locking up offenders, incarceration also has wider costs and consequences. Indirect costs include amongst other things extra support for the adolescent to reintegrate into the education system or the labour market and lost wages of parents due to the high time demands of an incarcerated child [1].

As a result of the unfavourable outcomes of incarceration, there is a strong need for evidence-based treatments that can provide an alternative to incarceration for youth with serious emotional and behavioural problems. Multisystemic Therapy (MST) has been proposed as a promising, cost-effective intervention for this group of young people. Several studies show significant reductions in number of serious crimes and days incarcerated [4-6]. However, research conducted in Canada and Sweden did not show significant differences in treatment effects between MST and care-as-usual (CAU) [7,8]. A review by Littell et al. [9] confirmed that the evidence regarding the superiority of MST compared to CAU is still inconclusive.

The introduction of an intensive family- and community-based treatment such as MST will always be associated with additional costs. Cost-effectiveness studies in child and youth care are required to provide decision makers with information on whether this intervention represents good value for money. Therefore, studies are needed that assess how well MST works – its influence on behaviour and the use of health and welfare services – and how much it costs. Cost-effectiveness analysis (CEA) is an approach that combines these requirements.

Cost-effectiveness has hardly been studied in child and youth care. MST is an example of a youth care intervention. Available studies on cost-effectiveness of MST for adolescents with antisocial behaviour revealed generally positive results, but direct translation of previous findings is not possible due to several factors. For example, the study of Klietz et al. (2010) did not include the full spectrum of youth care utilization in their cost-effectiveness analysis [10]. In addition, the study of Olsson (2009) focused only on the direct costs associated with serious behavioural problems and overlooked indirect costs such as productivity loss [11]. All these methodological differences across studies lead to an incomplete overview of costs of MST [11]. To illustrate: in the study of Olsson (2009), MST was found to cost more than double that estimated in the studies of Aos et al. (2004) and Schoenwald et al. (1996) [11,12].

The aim of the present study is to assess the balance between direct and indirect costs and effects of MST in the Netherlands as compared to Care-As-Usual for adolescents with serious behavioural problems.

## Methods

### Trial design

The design of this cost-effectiveness study will be described following the CONSORT statement [13]. The study is a supplement to an MST-effectiveness study [14], which concerns a randomized controlled trial (RCT) with a follow-up measurement after 6 months. Participants will be randomly assigned to one of the two groups: MST or Care-As-Usual (CAU). Data will be collected using a standardized self-report questionnaire in a face-to-face situation before treatment (T1), immediately after treatment (T2) and at follow up (T3; 6 months after treatment) among adolescents, parents/primary carers and therapists. Adolescents and their parents will both receive €10 for filling out the questionnaire. The Medical Ethics Committee of Utrecht University approved the study design, protocols, procedures and informed consent. Participation is voluntary and all participants are asked to provide written informed consent at T1.

### Recruitment

Participants will be recruited via three MST institutions spread over the Netherlands. The recruitment per organization will differ because of differences in the setting in which MST will be delivered. One MST organization is located in the North of the Netherlands; the other two locations are in the West of the Netherlands.

In *the North of the Netherlands*, the study population will consist of adolescents referred by family guardians of the Youth Care Office to the youth care program called “Do What Works”. This program consists of maximum six weeks secure residential care, followed by MST (Intervention) or FFT (Functional Family Therapy; Care-As-Usual). After the residential period, adolescents will be randomized to MST or to Care-As-Usual. At the same time, adolescents and their parents will be informed about the MST-effectiveness study and they will be asked for their informed consent. Upon mutual consent of the adolescent and the parents, a first appointment will be made before the start of MST or Care-As-Usual, in order to obtain written informed consent and to administer the first questionnaire.

The recruitment in *the Western part of the Netherlands* will be conducted via referring agencies such as Child Protection Council, juvenile judges, Bureaus Youth Care and local referral institutions. The referrers will inform the potential eligible juveniles and their families that a study will be conducted to investigate the effectiveness of youth care. If the families meet the inclusion criteria for MST according to the MST supervisors of the participating institutions, research procedures will be explained to the juveniles and their families, and their informed consent to participate in the study will be obtained by researchers.

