### Randomization

Immediately after referral (Western part of the Netherlands) or after the residential period (Northern part of the Netherlands), participants will be randomized to MST or CAU with the use of a computerized randomization program. This program will execute the randomization separately for each site. The ratio of randomization between MST and CAU will be 1:1.

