### Strengths and limitations

This study will contribute to the extension of scientific knowledge about economic evaluation in the field of child and youth care. This concerns the evaluation of the actual balance between costs and effects in a field of care where this has hardly ever been explored before, i.e. with very limited sources to derive costs of other outcome valuations from. The study will be conducted as part of a randomized controlled trial. By using such a design, it can be assumed that any confounding variables are cancelled out.

Furthermore, the study will be conducted as a multicentre trial. This will increase the generalizability of the study because this will lead to a large number of participants, different geographic locations and the ability to compare results among organizations. We will obtain both direct and indirect costs across the entire field of youth care. We will also include quality of life measures. To increase inclusion and prevent loss to follow up, all adolescents and parents will receive assistance in administering the questionnaires. Finally, most outcome variables will be assessed via two informants. Multi-informant assessment is recommended as a way to obtain a more complete picture of the adolescent than reliance on self- or parent-report alone [16].

Despite the strengths and innovative aspects of this cost-effectiveness study, there are some issues that our study is unable to take into account. First, follow-up is limited to a period of six months. To determine long-term effects of the intervention, there should be follow-up after a couple of years to assess the effects and costs when the adolescent is older. Second, it is to be expected that we will be dealing with a ‘difficult-to-reach”-population.

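### The pooled MST-versus-CAU effect and ICER average over comparators that differ by region, and the stated analysis neither uses the site strata nor shows the regional results

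*Protocol article*

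**What the plan says.** **North (Protocol article, Recruitment).** One site, with a fixed programme: "This program consists of maximum six weeks secure residential care, followed by MST (Intervention) or FFT (Functional Family Therapy; Care-As-Usual". Allocation comes after the residential stay: "After the residential period, adolescents will be randomized to MST or to Care-As-Usual".

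**West (Recruitment, Interventions, Randomization).** Two sites, recruiting through referring agencies, with no residential phase described. The general definition of CAU applies: "juvenile justice services, child welfare services, individual adolescent counselling and home-based social services (for instance, parental counselling". The article adds: "Also included and variably implemented across regions are recently developed, evidence-based services such as Functional Family Therapy (FFT"; MDFT is named alongside it.

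**Randomisation.** The timing differs by region: "Immediately after referral (Western part of the Netherlands) or after the residential period (Northern part of the Netherlands". Allocation is 1:1 and is generated separately at each site.

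**Analysis (Statistical analysis).** The between-group comparison is an unpaired t-test or Mann–Whitney U test on pre-post differences. Cost differences, overall and by cost category, get bootstrap intervals. ICERs divide incremental costs by incremental effects, and an acceptability curve gives "the probability that MST is cost-effective compared to usual care over a range of thresholds". No site or region term, stratum or subgroup appears.

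**Claimed strength (Strengths and limitations).** The multicentre design is said to offer "different geographic locations and the ability to compare results among organizations".

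**The concern.** An incremental ratio means something only relative to its comparator. In the North the comparator is one named family therapy, which the article itself counts among evidence-based services, and every participant has just left secure residential care. In the West it is whatever mix of services is available. One pooled effect and one pooled ICER combine these contrasts with weights set by how many families each region happens to recruit.

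Three consequences follow for a decision maker:

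- A null result could mean that MST does no better than FFT, or that it does no better than ordinary services. The planned output cannot distinguish these.
- The pooled ICER moves with the North's share of the sample, which is not stated.
- The comparison among organizations is presented as a strength, but no stated analysis carries it out, and the two-group tests named have no place for site.

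**Working it through.** **1. The plan's own figure.** Inputs from the Sample size section: d = 0.5, alpha 0.05 (taken as two-sided), power 0.80. Normal approximation: n = 2 × (1.960 + 0.842)² / 0.5² = 62.8, so 63 per group. The two-sample t-test gives 63.8, so 64. The stated 64 reproduces. The article also gives 81 for the same inputs; that discrepancy is a separate matter. At the planned 100 per arm, power for a common d = 0.5 is 94%. No allowance is made for effects that differ by region.

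**2. What the pooled effect estimates.** Let p be the North's share. With 1:1 allocation within each site, both arms have about the same share, so

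pooled d = p × d(North) + (1 − p) × d(West).

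**3. Scenarios.** The article gives neither p nor regional effects. All of the following is assumed: d(West) = 0.5; d(North) = 0.5, 0.2 or 0; p = 20%, 33% (one third) or 50%. Example: 1/3 × 0.2 + 2/3 × 0.5 = 0.40. Pooled power is the two-sample t-test at 100 per arm.

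| d(North) | Pooled d (p = 20 / 33 / 50%) | Pooled power | Interaction power |
|---|---|---|---|
| 0.5 | 0.50 / 0.50 / 0.50 | 94 / 94 / 94% | no difference to detect |
| 0.2 | 0.44 / 0.40 / 0.35 | 87 / 80 / 69% | 13 / 17 / 18% |
| 0 (extreme) | 0.40 / 0.33 / 0.25 | 80 / 65 / 42% | 29 / 39 / 42% |

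**4. Interaction power.** SE = sqrt(2/n(North) + 2/n(West)), with n per arm. At p = one third: sqrt(2/33.3 + 2/66.7) = 0.300. For a regional difference of 0.3: Φ(0.3/0.300 − 1.96) = Φ(−0.96) = 17%. For 0.5: Φ(0.5/0.300 − 1.96) = Φ(−0.29) = 39%.

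**5. Effect on the ICER.** The pooled ICER is a ratio of averages:

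[p × ΔC(North) + (1 − p) × ΔC(West)] / [p × ΔE(North) + (1 − p) × ΔE(West)].

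If, for illustration, the cost difference and the outcome SD are the same in both regions, pooled ICER / West ICER = 0.5 / pooled d. With d(North) = 0.2 this is 0.5/0.44 = 1.14, 0.5/0.40 = 1.25 or 0.5/0.35 = 1.43 as p goes from 20% to 50%. The North's own ratio would be 0.5/0.2 = 2.5 times the West's. The pooled ratio therefore changes with recruitment alone and describes neither region's ratio.

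**6. Precision by region.** Half-width of the 95% interval = 1.96 × sqrt(2/n), in SD units. At a 33% North share: West, 1.96 × sqrt(2/67) = 0.34; North, 1.96 × sqrt(2/33) = 0.48.

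**The case against.** The strongest reply is that the article asks a national question, at the end of its Background: MST in the Netherlands against care as usual. It defines CAU as existing care that varies by region, so FFT in the North is one declared form of CAU. Randomisation 1:1 within each site keeps region from confounding the pooled contrast. The residential stay precedes randomisation and is common to both arms, so it changes the population and setting but does not bias the comparison. All of this stands.

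A reader might infer that the trial's question is answered for neither setting. The documents do not support that: a valid average over the recruited mix is an answer to the question asked. A reader might also want to rest the usual-care conclusion on the West alone. That would redefine CAU against the Interventions section, which does not exclude FFT or MDFT in the West. It would also leave 67 per arm at a 33% North share, only three above 64 (3/67 = 4.5% room for loss) in a population that the article expects to be hard to reach. With equal effects, power would fall from 94% pooled to 82%.

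The power loss is also assumption-driven. A zero effect against FFT is one extreme, and no passage gives an effect against FFT.

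Finally, regional subgroups may sit in an analysis plan or parent protocol that is not shown. Their absence alone would be no finding. But the article does state its tests and its ICER method, and these ignore the randomisation strata and do not deliver the comparison it claims as a strength. That part stands.

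**Conclusion.** The point holds as one of interpretation and transportability, not of bias. The pooled estimate validly answers the national MST-versus-CAU question for the mix recruited. It averages over MST against FFT after residential care and MST against mixed services, depends on an unstated split, and cannot say which contrast drives a result.

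The size cannot be fixed from the article. Under the assumed scenarios, power at 100 per arm is 94% if effects are equal and 87%, 80% or 69% if the North effect is 0.2; the zero-effect extreme gives 80%, 65% or 42%. A formal test of regional difference would have about 13–42% power in the scenarios where one exists, so regional results can inform a reader but cannot settle the matter.

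**What to change.** In the Statistical analysis section:

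- Stratify the between-group analysis by site, and bootstrap within site (or region) and arm.
- Keep the pooled estimate as the main result, described as an average over the recruited CAU mix. Report the North/West split among those randomised and among the complete cost-effect pairs that enter the ICER.
- Prespecify descriptive region-specific effects, cost differences, ICERs and acceptability curves with intervals. Label the North contrast as MST versus FFT after residential care.
- Treat any arm-by-region interaction as exploratory, and say that its power is low.

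The cost is analysis wording and a few extra tables, with no new data. The downside is wide regional intervals: about ±0.34 SD in the West and ±0.48 SD in the North at an assumed 33% North share. The North interval is almost as wide on each side as the design effect of 0.5, so its ICER and curve should be presented as imprecise.
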